# Evaluation of collaborative oral health care planning between older adults and personnel from public dental care and municipal care organizations: a study protocol for a cluster-randomized controlled study in Sweden

**DOI:** 10.1186/s13063-025-08753-6

**Published:** 2025-02-18

**Keywords:** Healthy ageing, Integrated healthcare systems, Oral health, Patient-centred care, Work-integrated learning

## Abstract

**Background:**

Patient participation is key in person-centred care, emphasizing individual choices in treatment. Oral health, integral to overall well-being, is sometimes a neglected part of health. This intervention introduces a novel approach to strengthen person-centred care in homecare settings, employing collaborative, interprofessional teamwork and shared documentation across care organizations. This protocol outlines the design of a cluster-randomized controlled trial (RCT) in Sweden, comparing traditional oral assessments with an interorganizational, team-based oral health care planning model facilitated by a shared digital platform for documentation. The overall aim is to evaluate a person-centred interprofessional and interorganizational model for oral health care planning supported by a digital platform to enable healthy ageing.

**Methods/design:**

The intervention, co-designed with older adults, academic institutions, healthcare providers in public dental care, and municipal organizations, will undergo ethical approval. The RCT will randomize older adults, dental hygienists (DHs) and nursing assistants (NAs) into two groups. The intervention group will attend a two-day workshop on a person-centred, three-step team-based model, while the control group will continue using standard procedures. Thereafter, the three-step collaborative model will be compared to standard procedures. Primary outcomes will be measured using the Revised Oral Assessment Guide (ROAG) and the General Oral Health Assessment Index (GOHAI). Secondary outcomes include health economic evaluations, participation rates and quality of care assessments. Qualitative studies from theoretical perspectives of change and learning based on interviews with key stakeholders will be conducted in both the test and control groups.

**Discussion:**

Taking a co-produced approach where theory and practice shape the research iteratively, a person-centred health care planning model supported by a shared digital platform for home settings is evaluated. Anticipated outcomes include improved oral assessments and a deeper understanding of effective person-centred care practices. The co-produced approach of the intervention is also expected to further develop knowledge regarding co-production within domains of healthy ageing from an oral health perspective. As such, the intervention shapes and fosters co-produced person-centred care and healthy ageing.

**Trial registration:**

ClinicalTrials.gov NCT06310798. Registered on 13 March 2024.

## Background

Healthy ageing is defined as ‘the process of developing and maintaining the functional ability that enables wellbeing in older age’ [1] (p. 4). Functional ability includes the ability to learn and participate in making decisions. As people age with multiple chronic diseases, team-based, interprofessional collaboration is considered key for conducting person-centred care in home settings [2]. Collaborative long-term interventions explored in home settings where older adults and dental and nursing staff participate in health care planning are scarce. Oral health is one crucial but often neglected area in home settings [3]. Therefore, there is a need to develop innovative interprofessional workforce models to support healthy ageing from an oral health perspective [4, 5]. This project is a response to this need. The overall research question is: How can a new team-based work model facilitate person-centred collaboration through oral health care planning with older people in home settings?

### Introduction to current practice: dental care remuneration programme in Sweden

In Sweden, long-term care and home settings are typically work domains for municipal care staff (i.e. for example nurses, nursing assistants, physiotherapists and social workers). The municipal organization is mostly financed by Swedish taxes and the care offered for older adults is regulated by health care legislation and social care legislation. The most frail older adults are cared for in ordinary homes and not in nursing homes [6]. In dental care organizations in Sweden, citizens (> 23 years old) pay a large part of the dental care costs themselves but are offered an annual state-funded dental care allowance and there is also high-cost protection. In dental care organizations, professionals like dentists, dental hygienists and dental nurses work at dental clinics, mainly regulated by the dental care legislation. However, in Sweden, a dental care remuneration programme is offered for people in need of extensive long-term care [7]. The goal of the dental care remuneration programme is to promote oral health, quality of life and proper nutrition. The programme offers highly beneficial subsidized dental care and a yearly oral assessment to people in their homes; the care is provided both in long-term care settings and in homes.

In West Sweden, the yearly oral assessments are conducted by dental professionals, mainly dental hygienists (DHs), from the public dental care organization in older adult’s home settings. Approximately 3500 older adults in West Sweden (Region Västra Götaland) received an oral assessment within the dental care remuneration programme in home settings in 2022. A collaborative agreement recommends that the oral assessments, including oral health care planning, should be conducted cross organizations, including both dental and municipal care staff. Also, the oral health care planning should be documented on an oral care card. The oral care card is a paper-based protocol describing the oral status of the person within the dental care remuneration programme as well as listing recommendations for everyday oral care, including different oral care products and procedures. If the person needs dental treatment, that is also documented on the oral care card. However, reports show that municipal care staff (mainly nursing assistants [NAs] rarely participate in the oral assessments, and recommendations documented on the oral care cards are seldom integrated into the home care records [8, 9]. To our knowledge, there are no studies exploring the change and learning aspects of the interprofessional co-creation of oral health care plans in home settings within the context of a dental care remuneration programme.

### Oral health amongst older adults

Oral health is essential for quality of life [10, 11]. It affects the physical, social and mental well-being of people and communities [12]. Oral health enables vital daily functions, such as the ability to speak, smile, taste, chew and swallow. Older adults who have become frail generally have poor oral health [13–15]. Poor oral health has been associated with malnutrition [16], diabetes [17], aspiration pneumonia [18], and cardiovascular diseases [19]. Like most non-communicable diseases, oral conditions are chronic and socially patterned [20], indicating the need for collaboration between dental care and other healthcare organizations to enable person-centred care and healthy ageing. The fact that older adults often lose contact with dental care with increasing age [21] also supports this statement. Further, recent research shows that attitudes, knowledge and routines concerning oral health and oral care for older adults could be improved [3, 22–24].

### Shared decision-making in the context of healthy ageing

There is a nationwide call in Sweden for the provision of more person-centred and integrated care. The call has a strong base in national legislation [25] and is consistent with international guidelines and research [4, 26] that emphasize person-centred care, such as patient participation in decision-making regarding their care.

Shared decision-making (SDM) is described as a process in which a choice is made by the patient, significant others or both, along with one or more healthcare professionals [27, 28]. It has been described as the crux of person-centred care [29] and has been widely used in healthcare. When patients are involved in SDM, they experience more recognition and gain more knowledge regarding the decisions made [30]. SDM is initiated when difficult choices must be made amongst several options with several potential outcomes, which might be regarded differently from person to person. For example, in the context of oral health care planning in a home, it could be important to plan, in a methodological way, whether a person wants to receive assisted oral care. Also, if there is a need for dental treatment or follow-up, whether they prefer to schedule an appointment at home or at the dental care clinic. Through SDM, someone with a decisional conflict can be assisted in making a quality decision based on the best available evidence about the risks and benefits of options and what matters most to the person [31].

### Use of digital tools across organizational boundaries, facilitating person-centred, integrated care

In-home care, SDM is facilitated when health professionals work in teams and have access to common tools [32]. Several studies suggest that digital tools can contribute to enabling person-centred care [33–35]. Digital tools are seen as the intermediaries amongst healthcare professionals and older adults. However, professionals within diverse organizations do not have access to all information concerning the health status of older adults [36]. This might contribute to older adults receiving conflicting information from different care personnel. Also, different care professionals tend to focus on their own fields of expertise [37]. This implies that it is not enough to use digital tools to connect older adults with their care providers, but that it is also critical to link their care providers together as older adults inevitably move between them.

The transitions between care providers, especially those from different organizations, have been critical points of failure which have led to undesirable health outcomes [34]. Patients affected by such a lack of coordination have reported feelings of being lost in the system, frustration, disempowerment, and lack of trust [38]. The possibility to conduct integrated care, to coordinate and communicate amongst professionals within diverse professions and organizations involved in the same care processes, is often lacking [37, 39]. This results in fragmented care [39, 40].

Consequently, professionals might regard an older adult’s diagnosis and treatment without considering their relevant medical history or being able to acknowledge the complexity of the whole person during health care planning. If older adults’ health information is accessible, it becomes possible to personalize the care pathway for each individual, contributing to person-centred care. Therefore, the overall aim of this project is to evaluate a person-centred interprofessional and interorganizational model for oral health care planning supported by a digital platform to facilitate healthy ageing.

## Theoretical framework

The Knowledge To Action framework (KTA framework) [41] has been widely used within healthcare domains to assist innovative research projects being implemented into practice in a successful way. The KTA framework has two main components, knowledge creation and an action cycle, and it focuses on seven phases for the application of knowledge in practice settings (Fig. 1; Table 1).

**Fig. 1 Fig1:**
[figure not shown]
Knowledge To Action (KTA) framework according to Graham et al. [41]

**Table 1 Tab1:** Summary of the intervention, guided by the KTA framework [41]

Phase	Action	Outcome
I. Identifying the problem or gap that needs attention, and identifying, reviewing and selecting the knowledge that can solve that problem or gap	Through an interprofessional infrastructure between dental care and municipal care [9, 42], it was concluded that oral care cards were difficult to use in regard to coordination, patient safety, communication and ethical considerations	✔ The oral assessments within the dental care remuneration programme model and the oral care cards were tentatively revised into a team-based work-model based on learning and guiding each other ✔ A paper-based prototype for a digital interorganizational oral care card was created
II. Adapting or tailoring the knowledge to the local context	The new team-based work-model and oral care card prototype were tested [43, 44] in 24 ordinary homes of older adults [45]	Data from oral assessments were analysed through: ✔ Decisional needs assessment during interprofessional oral health planning [45]
III. Assessing barriers to and facilitators of knowledge use	Researcher ([name]) participated in a course at University of Ottawa, Canada, in clinical decision-making Systematic search, review and theory analysis regarding SDM in oral health domain [46]	✔ Common theories regarding interprofessional decision-making between dental care and healthcare were concluded to be lacking Knowledge and tools for decision-making during oral health care planning were integrated into the oral care card prototype

## Methods

### Procedure of intervention

From a theoretical understanding of interventions as depending on theory and practice, this intervention is inspired by Schön [47], who states that stakeholders, through reflection-in-action, contribute to both theory and practice in an iterative way. Therefore, the empirical base for this research is important, and stakeholders from multiple domains are included and invited to co-create and participate. Guided by the KTA framework [41], the first four phases describe actions that have already been conducted, while the three last action phases describe planned actions, evaluations and a plan for implementation. The randomized controlled trials are described in the sixth phase.

#### Phase I: Identifying the problem or gap that needs attention, and identifying, reviewing and selecting the knowledge that can solve that problem or gap

Within a collaborative project between dental and municipal care organizations (in Swedish; “the TAIK-project”), an interprofessional infrastructure was established for learning at work and being able to conduct joint oral health care planning, and to perform and follow up activities on an interorganizational level facilitated healthy ageing [8, 42, 48]. It was concluded that oral care cards were difficult to use within the dental care remuneration programme and that patient safety needed improvement [8, 9].

Two hypotheses were suggested:I.The dental care remuneration programme work-model could gain from including older adults and the NAs further in the oral assessments to facilitate person-centred, integrated care and healthy ageing, i.e. through collaborative learning and decision-making [49].II.The oral assessments would gain from being based on common validated instruments and shared digital tools, which could facilitate healthy ageing and improve the quality of care [32].

From the two hypotheses, the model for oral assessments within the dental care remuneration programme was tentatively revised to:I.Aspects of self-reported health, including oral health, by the older adults.II.The Revised Oral Assessments Guide (ROAG) [50] will be used to facilitate a learning environment (ROAG performed in collaboration between older adults, DHs and nursing staff). ROAG is a validated instrument used within municipal home healthcare by nurses and NAs. It was also included to provide a common language. When ROAG indicated difficulties regarding oral hygiene (= score 2 or 3 on ‘teeth’ or ‘gum’ within ROAG), the cause of the inability to manage oral hygiene tasks could be explored inspired by the Oral Hygiene Ability Instrument (OHAI) [51].III.Health care planning should be theoretically anchored, supported by the Ottawa shared decision-making framework [52], a well-cited theoretical framework which also includes the surrounding for decision-making, except for the person making the decision.

#### Phase II: Adapting or tailoring the knowledge to the local context

The new work-model and the prototype were tested in 24 interprofessional and interorganizational teams taking a socio-cultural approach [43, 44] in home settings in October–November 2022 in West Sweden. The work-model for the teams (1 older adult, 1 DH, 1 nurse) was supported by a digital prototype (paper-based mock-up) for oral assessments. In total 24 older adults, seven DHs and eight registered nurses in home healthcare participated [45].

#### Phase III: Assessing barriers to and facilitators of knowledge use

The testing of the work-model and digital prototype revealed that the collaborative decision-making phase of interprofessional oral health care planning was challenging. Therefore, one researcher within the project ([name]) participated in a course in clinical decision-making at the University of Ottawa. To better anchor the patient participation approach during decision-making in the oral assessments in the dental care remuneration programme, plans were made to integrate the Ottawa decision support framework into a new team-based work-model supported by a digital platform. Since the present documentation within the dental care remuneration programme revealed a lack of evidence-based recommendations, the planned digital tool will support and suggest evidence-based treatments derived from oral assessments at the individual level guided by Sweden’s national dental guidelines [51]. Complying with these suggestions will not be mandatory.

The participants in the 24 teams in home settings requested options for dental care visits—(i) mobile units in home settings, (ii) digital consultation or (iii) regular visits at the clinic. These options should be integrated into a future shared digital tool to facilitate better coordination. Also, the participants asked for options regarding assistance for oral care (i.e. reminders, assistance with the distribution of oral hygiene products or with the entire process of oral hygiene) to be inserted into a future digital tool.

#### Phase V: Monitoring the knowledge use

Further development of the digital platform is planned for 2024 within a collaborative sister project for innovation. For example, a lawyer will assist in enabling interorganizational documentation between dental care and municipal organizations. Also, a steering committee and a project group will plan and monitor the process of development and implementation.

#### Phase VI: Evaluating outcomes 

The evaluation of the revised team-based work-model assisted by a digital platform is planned to be conducted as a cluster-randomized controlled trial (RCT) (Fig. 2).

**Fig. 2 Fig2:**
[figure not shown]
Procedure of RCT

*The control group* will conduct oral assessments as per standard praxis: DHs, preferably in pair with a NA, perform an oral assessment on an older adult in home settings. Instruments used will be a mouth mirror, torch and oral care card—a paper where oral status and recommendations are documented. The following aspects are to be documented, visible caries or periodontitis, xerostomia, the oral hygiene products that the older adult use, and if the older adult goes on regular dental visits. If the older adult has pain in the mouth this is also documented, and a suggestion for booking time at the dental clinic is then recommended.

*The test group* will do oral assessments in teams of older adults, DH and NA. The following instruments will be used, a mouth mirror, a torch and a shared, digital platform. A three-step model is suggested – where subjective information is first documented in the digital, shared platform. Thereafter, valid instruments for oral assessments, understandable for all (ROAG; 48), will guide the participants. If there are notifications on problems with conducting oral hygiene, the reason for the problem will be investigated through a validated instrument, OHAI [51]. Finally, shared health care planning will be conducted based on the previous findings and the older adults’ preferences. If indicated, dental treatments will be recommended either through an established dental clinic or a mobile dental unit.

All participation within the RCT, both in terms of professionals and older adults, will be voluntary and the project will be ethically reviewed. In West Sweden, the public dental care organization (including 3200 dental care professionals) is responsible for performing all oral assessments within the dental care remuneration programme. This guarantees a large empirical base. A schedule of enrolment, interventions and assessments according to Standard Protocol Items: Recommendations for Interventional Trials (SPIRIT) reporting guidelines [53] is presented in Fig. 3.

**Fig. 3 Fig3:**
[figure not shown]
Schedule of enrolment, interventions, and assessments within the intervention

In pairs, DHs within public dental care organizations in West Sweden will be randomized into test and control groups. Due to potential geographical specificities, NAs within the same municipality as the test control DHs will be asked to participate. As such, the test group will consist of 16 DHs and 16 NAs. They will form teams of two, and each team will collaborate with 15 older adults to conduct oral assessments and health care planning in home settings. The control group will consist of 16 DHs where each DH will perform oral assessments according to the dental care remuneration programme – that is, they will conduct business as usual on 15 older adults each. It is not mandatory but recommended for NAs to participate in the oral assessments; therefore, the number of participating NAs within the control group is unknown. Inclusion criteria for the older adults are having home care and being registered for the dental care remuneration programme. Inclusion criteria for the DHs are that they (in addition to their clinical work in public dentistry) perform oral assessments within the dental care remuneration programme, and for the NAs to work in-home care. *Exclusion criteria* for older adults is to be younger than 65 years old. In total, 480 oral assessments and health care planning sessions will be performed within the RCT including 480 older adults, 32 DHs and 16 NAs (+ unknown number of NAs in the control group) (Fig. 2).

The test group will participate in a two-day course, where initially an informed consent form will be signed by all participants, thereafter they will practise:Oral assessments according to ROAG [50].Oral hygiene ability assessments according to OHAI [51].Oral health-related quality of life assessment with the GOHAI [54, 55].Shared decision-making according to ODSF [52].Using the digital platform.

The course will be both theoretical and practical with elements of reflection. Also, test group management within dental and municipal healthcare will participate in a common half-day course where they will learn about the intervention and the digital platform. A dialogue regarding obstacles and opportunities will facilitate a common understanding and the continued implementation process. They will also set common goals regarding how to support the intervention.

At baseline, six project coordinators (DHs) will collect informed consent forms from all participants, before the intervention. The six project coordinators will collect data and manage spontaneous reports of adverse events and other unintended effects of trial interventions. Empirical data will be collected. All older adults that participate will be enrolled in the dental care remuneration programme and in-home care. Participants within the test and control groups will answer on the following parameters at baseline, which will guide the evaluation.

At baseline:Empirical data (participant characteristics, i.e. sex and age).Mini mental state examination (MMSE-SR) [56].ROAG [50].GOHAI [54, 55].

*Primary outcomes* -* change from baseline to 12 months follow-up:*Older adults’ oral health status according to ROAG (50).Older adults’ self-perception of their oral health-related quality of life according to GOHAI [54, 55].

*Secondary outcomes*
SURE test [57] before and after health planning in oral assessments. The SURE test is based on four validated questions which describe the older adults’ uncertainty about which treatment to choose and aspects contributing to uncertainty about the benefits and risks of each option, what matters most to the older adults, support in making a choice and feeling sure about the best choice.Person-Centered Care Assessment Tool [58] to measure the professionals’ experience of the extent to which the care is experienced as being person-centred.All participants (DHs, NAs and older adults) will be measured by health-related quality of life according to EQ-5D-5L [59].OHAI [51], for measuring the ability to perform oral hygiene tasks. The OHAI should be used when indicated, when ROAG [50] shows 2 or 3 at the variables ‘teeth’ and ‘gum’, or if the older adult expresses concerns about difficulties with maintaining oral hygiene.

All scales will be measured in both the test and control groups (relation 1:1). Thereafter, test (n = 16 pairs of DHs and NAs) and control (*n* = 16 DHs and *n* = unknown NAs) groups will conduct 15 oral assessments each in home settings (Fig. 2). The DHs and NAs will individually rate their team performance level after each oral assessment from 1 to 10 (1 = very bad, 10 = excellent). Within the test group, options regarding dental care visits will be (i) regular dental care visits, (ii) digital consultation, (iii) mobile unit at home settings and (iv) doing nothing. Within the control group, the options regarding dental care visits will be ‘business as usual’, namely, (i) regular dental care visits, (ii) digital consultation or (iii) doing nothing.

Follow-up at 6 months:Retrospective records review: Number of records including oral health care aspects within municipal care. Number of older adults having established contact with dental care. Number of older adults having been scheduled for dental treatment at mobile dental units and what treatment has been conducted.The oral health care recommendations will be analysed and compared to existing evidence-based guidelines and recommendations [60].Older adults’ oral health status according to ROAG [50].Older adults’ self-perception of oral health according to GOHAI [54, 55].All participants’ (DHs, NAs and older adults) health-related quality of life according to EQ-5D-5L [61].

Follow-up at 12 months:Oral health status according to ROAG [50].Older adults’ self-perception of oral health according to GOHAI [54, 55].All participants’ (DHs, NAs and older adults) health-related quality of life according to EQ-5D-5L [61].Person-Centered Care Assessment Tool [58].

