### Data analysis

Descriptive data will be presented using the mean and standard deviation (SD) or median and interquartile range for numeric variables, as appropriate. Categorical variables will be presented in numbers and percentages. The efficacy evaluation will be conducted according to intention-to-treat, including randomized subjects analysed by randomized treatment. Missing data will be imputed using multiple imputation. Drop-outs will be summarized descriptively by the treatment group with at breakdown of reasons for withdrawal.

Statistical analyses will be performed with appropriate methods for cluster RCTs using mixed effects models with DH as a random effect to account for intra-cluster correlations. Numeric variables will be adjusted for baseline values, if applicable. All questionnaire scales will be treated as numeric in this regard. Results will be presented using the mean difference between groups with 95% confidence intervals. The primary endpoints (change in ROAG and GOHAI from baseline to 12-month follow-up) will be tested at significance level *α* = 2.5%, a two-sided test, retaining the type I error rate of the primary endpoints at the 5% level. All other tests will be two-sided and conducted at the 5% significance level. No interim analyses will be conducted.

A total of 32 DH (16 per group) and 480 older adults (240 per group) will be included to demonstrate a clinically meaningful difference of 1 unit in ROAG at 80% power, adjusted for baseline values. The following assumptions were made: SD of change scores from baseline values = 3 since the older adults as a group are heterogeneous [45]. Weak to moderate correlation between baseline values and change scores = 0.3, m = 15 older adults per DH, a weak intraclass correlation coefficient within clusters = 0.05, significance level *α* = 0.025, two-sided test, and 25% drop-out [59]. A weak intraclass correlation coefficient is expected since DH is a licensed profession in Sweden, and ROAG is a validated instrument which shows little intraclass difference over time in nursing care [62]. A blinded evaluation of the SD, correlation, and intraclass coefficient will be conducted when 6-month follow-up data has been retrieved for 50% of the planned study participants, with a possibility for sample size adaption if judged necessary. Sample size calculations were conducted using SAS/STAT® Software, Version 9.4 of the SAS System for Windows (SAS Institute Inc. Cary, NC, USA).

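### Test-arm staff sign consent after allocation is known, and the text does not place the older adults' selection, consent and baseline before disclosure, so recruitment bias is not excluded

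*Protocol article*

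**What the plan says.** The documents describe who is randomised, and who consents when, in four places.

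- **Unit of randomisation.** The abstract (Methods/design) says: "The RCT will randomize older adults, dental hygienists (DHs) and nursing assistants (NAs) into two groups". The Phase VI section says: "In pairs, DHs within public dental care organizations in West Sweden will be randomized into test and control groups".
- **Staff.** After the DHs are randomised, "NAs within the same municipality as the test control DHs will be asked to participate". The test arm is then described: "As such, the test group will consist of 16 DHs and 16 NAs". On consent, the same section says: "The test group will participate in a two-day course, where initially an informed consent form will be signed by all participants".
- **Older adults.** On how they enter: "They will form teams of two, and each team will collaborate with 15 older adults". Each control DH likewise assesses 15. On consent, the baseline paragraph says: "At baseline, six project coordinators (DHs) will collect informed consent forms from all participants, before the intervention". It then lists MMSE, ROAG and GOHAI as baseline measures for participants in both arms. Participation is voluntary for staff and older adults alike.
- **Analysis.** Data analysis describes intention-to-treat as "including randomized subjects analysed by randomized treatment" and adjusts numeric variables for baseline values where applicable.

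Trial status says that recruitment and randomisation start in September 2025 and does not give their order. Phase VII says that the test group is trained before the intervention.

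**The concern.** In a cluster trial, randomising the DHs makes the two groups of older adults comparable only if knowledge of the arm cannot influence who is approached, who agrees, or how the baseline is scored. If a DH's arm is known beforehand, a trained test DH may put forward different clients from those a usual-care DH would, and clients may accept or decline depending on what they are offered. Staff who learn that they face a two-day course may also decline, whereas control staff face no such burden.

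Adjusting for baseline ROAG or GOHAI deals only with the part of such a difference that those scores capture. It does not remove differences in motivation or willingness to accept help, and it is weakened if the baseline itself is scored with the arm known.

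**Working it through.** **Step 1: order of events for staff.** DHs are randomised; NAs are approached by reference to the DHs' municipality; the test arm (16 DHs, 16 NAs) is formed; that arm attends a course and signs consent at its start. No control-arm course is described. Test-arm staff consent therefore follows disclosure, as the text stands.

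**Step 2: order of events for older adults.** Their consent and data are collected by six coordinators at baseline, before the intervention. Training of the test arm is also placed before the intervention. Both can hold whether baseline comes before or after the course, and before or after allocation is known. The text fixes eligibility (home care, programme registration, 65 or over). It does not say who picks the 15 or by what rule.

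**Step 3: unit of randomisation.** The abstract randomises older adults, DHs and NAs. The Phase VI section randomises DHs only. Both cannot be right. If only DHs are randomised, no older adult is literally a randomised subject in the sense of the intention-to-treat sentence.

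**Step 4: what a given bias would do (illustration only).** The documents give no figure for the bias, so 0.10, 0.25 and 0.50 ROAG units are assumptions, meaning what is left after baseline adjustment.

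Inputs from Data analysis: SD of change 3, correlation 0.3, ICC 0.05, 15 per DH, 240 per arm, 25% drop-out, two-sided alpha 0.025, target difference 1 unit.

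- Evaluable per arm: 240 × 0.75 = 180; per DH: 15 × 0.75 = 11.25
- Adjusted SD: 3 × √(1 − 0.3²) = 2.862
- Design effect: 1 + (11.25 − 1) × 0.05 = 1.5125
- SE: 2.862 × √(2 × 1.5125 / 180) = 0.371
- Critical value: 2.2414
- Rejection probability with no true effect and bias b: 1 − Φ(2.2414 − b/SE) + Φ(−2.2414 − b/SE)

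The plan's own claim of 80% power for 1 unit implies a smaller SE: 1 / (2.2414 + 0.8416) = 0.324. Both are shown.

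| Assumed bias (ROAG units) | Type I error, SE 0.371 | Type I error, SE 0.324 |
|---|---|---|
| 0 | 2.5% | 2.5% |
| 0.10 | 3.0% | 3.2% |
| 0.25 | 6.0% | 7.2% |
| 0.50 | 18.6% | 24.2% |

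The two SEs differ because the stated total of 480 is not reproduced from the stated inputs by the standard formula: the SE of 0.371 corresponds to 67.5% power, and the same approach would need 628 in total. That is a separate matter, and the present point does not depend on it.

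**The case against.** A reader might infer that the older adults are selected, consented and measured after the allocation is disclosed. The documents do not establish this. The course consent concerns the test group, listed there as DHs and NAs, so it says nothing about older adults. Their consent is assigned to the coordinators, and baseline is not said to be scored by the treating DHs. The schedule of enrolment (Fig. 3) and the trial procedure (Fig. 2) are not visible in the text at hand and may show the order, and an article condenses a fuller protocol.

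Other points on that side also carry weight. Eligibility rests on objective criteria. MMSE is taken at baseline, so an imbalance in cognition could be seen and adjusted for. The two consent statements can both be true if staff sign at the course and coordinators collect the older adults' forms. In a trial labelled cluster-randomised with DH as a random effect, the intention-to-treat sentence would ordinarily be read as older adults analysed by their DH's allocation. The bias sizes above are assumed.

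What this does not answer: staff consent in the test arm follows allocation on the plain text; the abstract contradicts the body on who is randomised; and nothing visible puts the older adults' identification, consent or baseline ahead of disclosure.

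**Conclusion.** The point holds in this form: the plan has test-arm staff consent after their arm is known, and its visible text does not secure that older adults are identified, consented and measured before disclosure. Followed as written, it permits arm-dependent enrolment of volunteers. It does not show that such enrolment will happen.

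The size of any bias cannot be derived from the documents. Under the assumed sizes, a residual bias of a quarter of the 1-unit target difference would more than double the 2.5% error for ROAG. This rests on a normal approximation and the plan's own SD, correlation, ICC and drop-out. The statement in the abstract that older adults are randomised is an error against the body and blurs the intention-to-treat wording. The matter should be settled before recruitment starts; if the safe order is already intended, a sentence stating it would settle the older adults' part.

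**What to change.** 1. Obtain DH consent before randomisation and, where feasible, consent of the NAs who would form test teams. NA participation in the control arm is optional and of unknown extent, so this may not be fully achievable for NAs.
2. For each DH, list the eligible programme-registered home-care clients aged 65 or over and draw the older adults consecutively or at random from that list.
3. Have the coordinators take older adults' consent and baseline ROAG and GOHAI before that DH's allocation is released. If pairs of DHs are split between arms, releasing one reveals the other, so both lists should be complete first. If this order is not feasible, use a recruiter and assessor among the coordinators who is unaware of allocation.
4. Reconcile the abstract, the Phase VI text on randomisation and consent, and the Data analysis section, so that DHs are the randomised unit and older adults are analysed by their DH's allocation.

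The cost is small but real. Existing coordinators and programme registers suffice. Some older adults will be lost between listing and visit, and the course will start slightly later, in a calendar that runs from September 2025 to September 2026 with a 12-month endpoint and so has little slack.
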